# Efficacy of intra-articular injection of allogeneic platelet-rich plasma for knee osteoarthritis combined with hematologic blood dyscrasias with platelet dysfunction: protocol of a randomized, double-blind, placebo-controlled trial

**DOI:** 10.1186/s12891-022-06073-3

**Published:** 2022-12-14

**Keywords:** Allogeneic platelet-rich plasma, Knee osteoarthritis, Hematologic blood dyscrasias, Platelet dysfunction, Clinical trial

## Abstract

**Background:**

Autologous platelet-rich plasma (PRP) has been shown to alleviate the symptoms of patients suffering from knee osteoarthritis (KOA), but for certain patients with hematologic diseases with platelet dysfunction and patients receiving anti-platelet medications, autologous PRP is not an optimum solution. Allogeneic PRP has been proven to be safe and effective in the treatment of osteoarthritis, rotator cuff disease, refractory wounds and other medical fields. However, a well-designed and long-term follow-up prospective randomized controlled trial (RCT) to evaluate the effect of allogeneic PRP intra-articular injections for KOA combined with hematologic blood dyscrasias has not yet been performed.

**Methods/ design:**

We will conduct an allogeneic PRP injection for KOA combined with hematologic blood dyscrasias with platelet dysfunction study: a prospective, randomized, double-blind, placebo-controlled trial. One hundred participants with KOA combined with hematologic blood dyscrasias with platelet dysfunction will be randomly allocated to receive either one allogeneic PRP injection or one saline injection into the knee joint. The primary outcome will be a 12-month change in Western Ontario and McMaster Universities Osteoarthritis Index (WOMAC) score. Secondary outcomes will be the 36-Item Short-Form General Health Survey (SF-36) score, Lysholm score, overall knee pain score and MRI assessment at 1-, 3-, 6- and 12-month.

**Discussion:**

The results of this study will help determine whether allogeneic PRP could be used as a non-surgical intervention to treat patients with knee OA combined with hematologic blood dyscrasias with platelet dysfunction.

**Trial registration:**

Chinese Clinical Trials Registry reference: ChiCTR2100048624. Prospectively registered 11th of July 2021.

**Supplementary Information:**

The online version contains supplementary material available at 10.1186/s12891-022-06073-3.

## Background

Generally, knee osteoarthritis (KOA) is the most common cause of knee pain and dysfunction in the elderly. Osteoarthritis usually affects the medial compartment of the knee joint, which is related to misalignment. Currently, most research has focused on the treatment of pain relief and prevention of decline in function [1, 2].

Autologous platelet-rich plasma (PRP) is a safe autologous blood product containing high levels of growth factors and cytokines with potential to alter biological processes implicated in OA pathogenesis and symptoms [3]. In addition, several studies have reported that compared with non-steroidal anti-inflammatory drugs (NSAIDs), steroid and hyaluronic acid, PRP has favorable pain and function outcomes, [4–6] suggesting the potential benefits of PRP in treating KOA. Some alternative physical therapy, such as low-level laser therapy, needs to be further confirmed for efficacy in KOA patients [7].

Recent systematic reviews concluded that platelet dysfunction might have an impact on the efficacy of PRP [8]. For certain patients with hematological diseases (e.g. immune thrombocytopenia, aplastic anemia, systemic lupus erythematosus, etc.) and patients receiving anti-platelet medications, autologous PRP is not an optimum solution. Allogeneic platelet-rich plasma has been shown to be safe and effective in treating osteoarthritis, rotator cuff dysfunction, refractory wounds, and other medical fields [9–12]. Given the clinical effect on pain reduction in osteoarthritis and a good safety profile, allogeneic PRP is a promising nonsurgical therapy for knee OA combined with hematologic blood dyscrasias with platelet dysfunction. However, clinical trials of efficacy to date have been limited by a high risk of bias in allogeneic PRP trials. Although the results show that allogeneic PRP is safe and can relieve pain and recover articular function, the trials lack adequate blinding and control group suggesting the results are not convincing [11, 12]. Well-designed and long-term follow-up prospective randomized controlled trials (RCTs) have not yet been performed.

The aim of this study is to evaluate the safety and efficacy of intra-articular injection of allogeneic PRP from blood donors in patients with knee osteoarthritis combined with hematologic blood dyscrasias with platelet dysfunction. (e.g. immune thrombocytopenia, aplastic anemia, etc.) Our hypothesis is that there is a clinically relevant difference in the primary and secondary outcomes between the two treatment groups. The minimal clinically important differences of patient reported outcomes will be considered in this study.

## Method/design

### Trial design

The allogeneic PRP injection for knee OA study is a prospective, randomized, double-blind, placebo-controlled trial design. This study protocol follows the recommendations of the SPIRIT Statement (supplement 1) [13] for clinical trial protocols elaboration and is reported according to the CONSORT Statement (supplement 2) [14]. The trial will be conducted at The First Affiliated Hospital of Soochow University, which is one of the three national clinical research centers for hematologic disease in China. The primary endpoint for the analysis of outcomes is 12 months after baseline assessment. The trial is registered at the Chinese Clinical Trial Registry with a number of ChiCTR2100048624 and follows the World Health Organization’s guidelines.

### Participants

We will recruit 100 participants with painful knee OA combined with hematologic blood dyscrasias with platelet dysfunction from outpatient department. Participants are eligible for the study if they meet all inclusion criteria below:i.age between 18 and 80 yearsii.unilateral symptomatic knee with history of chronic pain (at least 4 months) or swellingiii.hematologic blood dyscrasias with platelet dysfunctioniv.limitation of daily activitiesv.radiographic imaging findings of knee osteoarthritis (Kellgren and Lawrence grade 1–3)

The exclusion criteria are as follows:i.systemic cardiovascular or neurologic disorders, diabetes septicemia or feverii.cutaneous infections in the area to be injectediii.had injection into the target knee joint of glucocorticoid in the past 3 months or hyaluronic acid in the past 6 monthsiv.use of nonsteroidal anti-inflammatory drugs (NSAIDs) within 5 days before treatmentv.previous knee surgeryvi.have systemic or inflammatory joint disease such as rheumatoid arthritisvii.have other muscular or joint affecting lower limb function

### Procedures

Figure 1 and Table 1 outline the trial phases and the schedule for enrollment, screening, interventions and assessments. Participants will complete an onsite survey in the outpatient department to determine initial qualifications, and then a coordinating researcher will screen through a questionnaire. Participants deemed appropriate from the questionnaire screening will be allowed to undergo conventional radiographs (weight-bearing long-leg, A/P and lateral views) and blood screening. The screening will be performed in the outpatient department, where two experienced physicians evaluated patients’ eligibility for enrollment in this study through history taking, imaging examination, and laboratory tests. These steps could diminish possible bias about the inclusion criteria of age range. Participants who meet the inclusion and exclusion criteria will then be deemed suitable for the study. Eligible participants will complete the baseline clinical outcome scores, paper-based questionnaires and baseline knee MRI scans. Participants will also be asked to discontinue non-steroidal anti-inflammatory drugs and other analgesics for knee pain from 3 weeks before the baseline assessment until the 12-month follow-up assessment.

**Fig. 1 Fig1:**
[figure not shown]
Flow diagram of the study protocol

**Table 1 Tab1:** Schedule of enrolment, interventions and assessments

Time point			Study period				
	Enrolment	Baseline	Injection	Post-allocation			Close-out
			1	1 M	3 M	6 M	12 M
**Enrolment**							
**Eligibility screen**	**×**						
**Informed consent**	**×**						
**Allocation**		**×**					
**Interventions:**							
**Platelet rich plasma**			**×**				
**Saline**			**×**				
**Assessments:**							
**Primary outcomes**							
^**a**^**WOMAC score**		**×**		**×**	**×**	**×**	**×**
**Secondary outcomes**							
^**b**^**VAS**		**×**		**×**	**×**	**×**	**×**
**Lysholm score**		**×**		**×**	**×**	**×**	**×**
^**c**^**SF-36**		**×**		**×**	**×**	**×**	**×**
**MRI analysis**		**×**					**×**
**Other measures**							
**Drug/supplement use**		**×**		**×**	**×**	**×**	**×**
**Platelets and leukocytes counts, VEGF and TGF-β**			**×**				
**Number of injections**			**×**				
**Adverse events**			**×**	**×**	**×**	**×**	**×**
**Success of blinding**			**×**				
**Descriptive measures**							
**Weight, height, BMI, Kellgren and Lawrence grade, Age, gender, duration of symptoms**		**×**					
**Injection site, Complications**			**×**				

^a^WOMAC score, The Western Ontario and McMaster Universities Osteoarthritis Index; ^b^VAS, visual analogue scale; ^c^SF-36, the short-form 36 item health survey questionnaire

Paper-based clinical outcome scores will be distributed to participants at 1-, 3-, 6-, and 12-month to complete primary and secondary outcomes at the outpatient department. Knee MRI scans will be conducted at 12-month at the radiology center of the First Affiliated Hospital of Soochow University. At the last follow-up, patients will be asked if they would like to receive allogeneic PRP injection again. This will be registered accordingly.

### Monitoring committee

The trial will be monitored by the clinical research monitoring committee of the First Affiliated Hospital of Soochow University. The monitoring committee aims to improve the quality of clinical research and ultimately, patient care. Before the trial commenced, a monitoring plan was set up. Monitors will be required to verify that:the conduct of the trial is compliant with the currently approved protocol and with applicable laws regulatory requirements, for example, WMO, GCP (China), ISO14155 and laws on clinical research in China;the rights and privacy of patient subjects are protected;The research data is accurate, complete, and true.

Monitoring will be performed at the initiation of the study until the results of the study are published.

### Randomization procedures

Randomization is centralized, and participants will be randomly allocated in a 1:1 ratio. An independent statistician will provide a computer-generated randomization list, using a permuted block design with block sizes of 4 and 6. The sequence is concealed by the use of a computer interface implemented in the electronic case report form. The patients, treating physicians and coordinating researchers will all be blinded to the allocation of the intervention. A study nurse will have access to the randomization result and the allocated intervention.

### Blinding arrangements

Participants will not be told until the end of the study which group they were allocated to. The study nurse will prepare the injection in a separate room and place an opaque label around the syringe and needle base to mask the contents. The nurse will then give the syringe to the injecting treating physician who will not know or be able to tell whether the syringe has allogeneic PRP or saline. All clinical and MRI assessments will be conducted by two radiologists with over 10 years of clinical work experience. All evaluators are blinded to treatment allocation.

### Interventions

Participants in both the allogeneic PRP and saline groups will receive one intra-articular knee injection at the same time after signing written informed consent (supplement 3), in line with commonly used injection protocols for this condition [6, 15]. The study nurse will give the treating physician an occluded syringe with a needle containing 4 ml of either normal saline or allogeneic PRP, and the contents will be injected into the knee joint. After the injection, passive knee flexion and extension will be performed six times with the participant observed resting for 20 min thereafter.

After injection, participants will be asked which group they believe they are in, and separately the injecting treating physician will also be asked which group they believe the participant is in to assess the success of blinding. This will be registered accordingly. The study nurse will ask the participant if they experienced any adverse events following the injection.

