### Safety

All adverse events are reported spontaneously by the patient or observed by the study nurse. This will include questions about any adverse events that participants believe may be related to the trial intervention, including their nature, how long they lasted for and what action if any, they took. To date, no serious adverse events have been reported in the literature concerning PRP intra-articular injections of the knee. The local Medical Ethical Commission will be notified of any serious adverse events. In the event this happens, the advice of the Medical Ethical Commission will be followed accordingly.

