### Loss to follow-up

The coordinating researchers will attempt to reduce loss to follow-up as much as possible by contacting every patient and being present at every patient visit. Each patient will be assisted by a coordinating researcher to ensure that each paper-based questionnaire is filled in. If the patient is lost to follow-up, an analysis of demographic and prognostic characteristics will be performed on these cases and the remaining patients. The patient eligible for and compliant with each follow-up will be documented.

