### Data management

Paper-based questionnaires will be the primary data collection tools for the study. The questionnaires will be completed at the outpatient clinic at baseline and each follow-up time point. On receipt of the questionnaire forms, the coordinating researchers will make a visual check of the responses and query missing data when possible. The paper-based questionnaire will be securely kept by a study nurse.

A study nurse, blinded to the group allocation, will store the forms into an electronic database by double data entry to minimise typing errors. The coordinating researchers, blinded to the group allocation, will perform a visual check of the data in the electronic database and then query all missing, implausible and inconsistent data. Patient records in the participating hospitals will be used when collecting missing data or interpreting inconsistent or implausible data.

After 12-month follow-up visits are completed and all data stored, a research assistant, not involved in the trial, will aggregate all the data into a separate database, which will be the source for the final data analysis. Participant files will be maintained in storage (both in electronic and paper formats) at the coordinating center for a period of 10 years after completion of the study (10-year follow-up visits).

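### The study nurse who knows the allocation also asks about and observes adverse events, and the Safety section does not settle which events are asked about

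*Protocol article*

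**What the plan says.** - **Who knows the allocation.** Randomization procedures lists those kept blind: "The patients, treating physicians and coordinating researchers will all be blinded to the allocation of the intervention". It continues: "A study nurse will have access to the randomization result and the allocated intervention". Blinding arrangements, PRP preparation and Saline injections give syringe preparation to the study nurse, who therefore knows the contents. Blinding arrangements also says that evaluators do not know the treatment.
- **Who collects adverse events.** Interventions: "The study nurse will ask the participant if they experienced any adverse events following the injection". Safety: "All adverse events are reported spontaneously by the patient or observed by the study nurse".
- **Which events.** The next sentence of Safety says that collection will include questions on "any adverse events that participants believe may be related to the trial intervention".
- **When.** Table 1 schedules adverse events at the injection and at 1, 3, 6 and 12 months.
- **A nurse described as blinded.** Data management: "A study nurse, blinded to the group allocation, will store the forms into an electronic database".
- **Who else is present.** Under Loss to follow-up, the coordinating researchers commit to "contacting every patient and being present at every patient visit".
- **Status of safety.** Background: "The aim of this study is to evaluate the safety and efficacy of intra-articular injection of allogeneic PRP".

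**The concern.** Adverse events depend heavily on how they are sought. How a question is put, how far an answer is followed up and whether a minor complaint is written down can all shift when the questioner knows what was injected. A saline arm lets causality be judged by comparing arms, and that comparison is fair only if events are sought equally in both. Here the only role that is given the allocation is also the only role named as asking about or observing adverse events. Safety is half of the stated aim, and Ethics and dissemination says the results will inform practice on safety. Uneven ascertainment cannot be repaired at the analysis stage.

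A second, smaller problem is scope. If questions at the later visits centre on events that participants themselves attribute to the injection, events with no obvious link to it may go unrecorded. Those are the events for which the comparison between arms is most needed.

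**Working it through.** The plan states no adverse event figure to reproduce, so the check sets the sections against each other.

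1. **Does the person who asks know the allocation?** Randomization procedures introduces a study nurse with allocation access. Blinding arrangements, PRP preparation and Saline injections assign the syringes to the study nurse. Interventions has the study nurse hand over the syringe and, later in the same section, ask about adverse events. Nothing signals a change of person. As written, the answer is yes.

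2. **Does another section supply a blinded adverse event collector?** Data management has a blinded nurse, but for entering forms, with no adverse event task. Safety names the study nurse as observer. No blinded person is assigned.

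3. **Is this consistent with the blinding statement?** If evaluators include whoever assesses safety, steps 1 and 2 contradict Blinding arrangements.

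4. **Is the scope of the questions settled?** There are two mismatches:
   - The first sentence of Safety makes every event either spontaneous or observed, but the second describes questions.
   - Interventions asks an open question with no reference to cause. Safety describes questions on events believed to be related. The open question is tied to the injection, so for 1 to 12 months the only questions described are those in Safety, and the section does not say who asks them.

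5. **Illustration of size, on assumed values only.** Let *p* be the true proportion with an event, equal in both arms, and let *a* and *b* be the fractions recorded in the two arms. The spurious difference is *p*(*a* − *b*) and the spurious ratio is *a*/*b*.

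| *p* | *a* = 1.0, *b* = 0.8 | *a* = 1.0, *b* = 0.6 |
|---|---|---|
| 0.10 | 0.10 × 0.2 = 2 points | 0.10 × 0.4 = 4 points |
| 0.20 | 0.20 × 0.2 = 4 points | 0.20 × 0.4 = 8 points |
| 0.30 | 0.30 × 0.2 = 6 points | 0.30 × 0.4 = 12 points |
| Ratio | 1/0.8 = 1.25 | 1/0.6 = 1.67 |

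None of these values of *p*, *a* or *b* comes from the document, and the direction of the bias is unknown. The table treats all events as subject to uneven recording, so any share reported spontaneously makes the effect smaller.

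**The case against.** The other side has several good arguments.

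- **Filtering.** A reader might infer that only events thought to be related are recorded. The text does not say so. Safety says collection will include such questions, without limiting it to them. It also admits spontaneous reports and observation, and the question in Interventions is open. What stands is unclear wording, not a proven filter.
- **All safety data unblinded.** A reader might infer this too. Spontaneous reports come from blinded patients, and no section says the nurse questions participants at 1 to 12 months. Only the nurse-elicited and nurse-observed part is exposed.
- **Unblinding the participant.** One might suspect that the nurse could reveal the arm before participants guess their group. Interventions describes the guess first and the nurse's question afterwards, and nothing suggests disclosure. This is not supported.
- **One nurse both blinded and unblinded.** Randomization procedures and Data management each refer to a nurse with an indefinite article, so two people may well be meant. This needs a clarifying phrase and is not a demonstrated contradiction.
- **Meaning of evaluators.** The sentence follows one about radiologists carrying out the clinical and MRI assessments, so it may cover only them. On that reading the literal conflict goes, but adverse events are still sought by someone who knows the allocation in a trial described as double-blind.
- **Weight.** Table 1 lists adverse events under other measures, and WOMAC forms are completed by blinded patients. This is right and limits the severity. It does not remove the problem, because safety is a stated aim.

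**Conclusion.** The point holds in a limited form. Followed as written, the protocol has the nurse who knows the allocation ask about adverse events after injection and observe them. That part of the safety data is open to uneven ascertainment between arms. The Safety section is also internally unclear on whether events are asked for, and narrower in scope than the question in Interventions.

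The conclusion assumes that the study nurse in Interventions and Safety is the one given the allocation in Randomization procedures, which is the plain reading. The bias cannot be sized from the document, and the 2 to 12 points above only show what assumed recording rates would produce. It would also be wrong to present the wide uncertainty of a zero count in 50 patients as the size of this defect, since that applies to any arm of 50 however events are collected.

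Severity is moderate: a stated aim is exposed, but the primary WOMAC analysis is not.

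**What to change.** - Have a blinded coordinating researcher elicit and record all adverse events, using the open question in Interventions, at the injection and at 1, 3, 6 and 12 months, whatever the participant thinks caused them.
- Restrict the nurse with allocation access to preparing and handing over syringes.
- Reword Interventions and Safety to match. Say that events are asked for as well as reported spontaneously, and name who asks.
- State in Data management that the blinded data-entry nurse is not the nurse with allocation access.

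The coordinating researchers are already blinded and due at every visit, so no visits or staff are added. The cost is a reassignment of tasks, some rewording and somewhat more adverse event records to process.

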### PRP preparation

One healthy volunteer donor will donate about 300–400 ml (according to the definite number of participants) of peripheral venous blood. To assess the safety of the allogeneic PRP, tests for hepatitis B, hepatitis C, human immunodeficiency virus, and syphilis will be performed and confirmed before application. Every 8 ml of venous blood for each participant (as recommended by the company) is drawn manually using butterfly safety locks and emptied into 10-ml standard tubes (Regenlab PRP Kit-RegenACR®, Le Mont-sur-Lausanne, Switzerland) and are then put in RegenLab PRP Centrifuges. The centrifugation settings are set at 1500 g for 5 minutes. After centrifugation, the blood is fractionated. By gently inverting the Regen BCT tubes several times and process for resuspension of the cellular deposit in the supernatant, approximately 4 ml of PRP will be obtained from each tube. The PRP used for injection will not be activated before application. About 4 ml of PRP will be injected for each patient in the PRP group. In addition, one tube of PRP will be sent to the laboratory for platelet and leukocyte counting, and growth factor (VEGF and TGF-β) analysis. The whole process will be carried out by a study nurse in a separate room and the syringe and needle base will be placed an opaque label to mask the contents.

